**LIST OF ABBREVIATIONS AND RELEVANT DEFINITIONS**

|                |                                                                                                                                                                                                                               |
|----------------|-------------------------------------------------------------------------------------------------------------------------------------------------------------------------------------------------------------------------------|
| ABR     | General Assessment and Registration form (ABR form), the application form that is required for submission to the accredited Ethics Committee; in Dutch: Algemeen Beoordelings- en Registratieformulier (ABR-formulier) |
| AE      | Adverse Event                                                                                                                                                                                                          |
| AR      | Adverse Reaction                                                                                                                                                                                                       |
| CA      | Competent Authority                                                                                                                                                                                                    |
| CCMO    | Central Committee on Research Involving Human Subjects; in Dutch: Centrale Commissie Mensgebonden Onderzoek                                                                                                            |
| CV      | Curriculum Vitae                                                                                                                                                                                                       |
| DSMB    | Data Safety Monitoring Board                                                                                                                                                                                           |
|                | European Union                                                                                                                                                                                                         |
| EMDR    | Eye Movement Desentization and Reprocessing                                                                                                                                                                            |
| EU      |                                                                                                                                                                                                                               |
| EudraCT | European drug regulatory affairs Clinical Trials                                                                                                                                                                       |
| GCP     | Good Clinical Practice                                                                                                                                                                                                 |
| GDPR    | General Data Protection Regulation; in Dutch: Algemene Verordening Gegevensbescherming (AVG)                                                                                                                           |
| IB      | Investigator's Brochure                                                                                                                                                                                                |
| IC      | Informed Consent                                                                                                                                                                                                       |
| IMP     | Investigational Medicinal Product                                                                                                                                                                                      |
| IMPD    | Investigational Medicinal Product Dossier                                                                                                                                                                              |
| METC    | Medical research ethics committee (MREC); in Dutch: medisch-ethische toetsingscommissie (METC)                                                                                                                         |
| PD      | Personality Disorder                                                                                                                                                                                                   |
| PTSD    | Posttraumatic Stress Disorder                                                                                                                                                                                          |
| RCT     | Randomized controlled trial                                                                                                                                                                                            |
| (S)AE   | (Serious) Adverse Event                                                                                                                                                                                                |
| SPC     | Summary of Product Characteristics; in Dutch: officiële productinformatie IB1-tekst                                                                                                                                    |
| Sponsor | The sponsor is the party that commissions the organisation or performance of the research, for example a pharmaceutical                                                                                                |

company, academic hospital, scientific organisation or investigator. A party that provides funding for a study but does not commission it is not regarded as the sponsor, but referred to as a subsidising party.

**UAVG** Dutch Act on Implementation of the General Data Protection Regulation; in Dutch: Uitvoeringswet AVG

**WMO** Medical Research Involving Human Subjects Act; in Dutch: Wet Medisch-wetenschappelijk Onderzoek met Mensen

## SUMMARY

**Rationale:** There is evidence suggesting that EMDR therapy is not only effective in the treatment of patients with personality disorders (PD) with and without PTSD, but also efficient, and thus cost-effective. Interventions for PD have a long duration and approximately 50% does not benefit sufficiently. The next step is to conduct a RCT for patients with all types of PD to explore the efficacy and cost-effectiveness of EMDR compared to waiting list to confirm these preliminary results.

**Objective:** The aim of this study is to evaluate the effectiveness of EMDR in reducing PD symptoms.

**Study design:** A multicenter, single-blind randomized controlled trial (RCT) with two arms: EMDR and no treatment (waiting list).

**Study population:** Patients with PD of eighteen years or older

**Intervention (if applicable):** The Dutch version of the standard EMDR protocol (de Jongh & ten Broeke, 2019) will be used. The protocol will focus on the most distressing target memory. A total of 10 biweekly sessions of EMDR will be applied with a duration of 90 minutes per session.

**Main study parameters/endpoints:** Mixed models, cost-utility and –effectiveness analyses will be conducted. The following outcome measures will be used: The Assessment van DSM Persoonlijkheidsstoornissen-IV and Clinician-Administered PTSD Scale for DSM-5 (primary outcomes) and the Structured Clinical Interview for DSM 5 Personality Disorders, Jeugd Trauma Vragenlijst, Life Events Checklist for the DSM-5, Level of Personality Functioning Scale - Brief Form 2.0, Clinician-Administered PTSD Scale for DSM-5, PTSD Check List, , Difficulties in Emotion Regulation Scale, Brief State Paranoia Checklist, Outcome Questionnaire-45, Euro-Quality of Life 5 dimension 5 level version, Treatment inventory Cost In Psychiatric Patients, Mental Health Quality of Life questionnaire.

Data will be collected at baseline, 5 week (post EMDR-treatment) and 3, 6 and 12 months after onset of the study.

**Nature and extent of the burden and risks associated with participation, benefit and group relatedness:** It is expected that patients who receive EMDR, will experience a reduction in PD- and PTSD-symptoms and an improvement in quality of life and interpersonal functioning. In addition, EMDR is safe and not associated with adverse events. The study requires participants in the control group to not receive treatment for three months. In the two or three days after an EMDR-session symptoms of emotion dysregulation or psychotrauma may increase. This effect is temporarily and not associated with any increase in selfinjurious – or suicidal behavior.

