## 2. OBJECTIVES

### *Primary Objectives:*

- 1) How effective is EMDR therapy compared to waiting list on symptoms of PD?
- 2) How cost-effective is EMDR therapy versus a wait-list control condition?

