### *Secondary Objectives:*

- 3) What is the decline in the proportion of patients fulfilling a diagnosis of PD after EMDR?
- 4) How effective is EMDR therapy compared to waiting list on the severity of symptoms of PTSD?
- 5) How effective is EMDR therapy on mental health outcome, severity of difficulties in emotion regulation and interpersonal functioning?
- 6) What is the effectiveness of EMDR on quality of life?

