## 8. METHODS

### 8.1 Study parameters/endpoints

#### 8.1.1 Main study parameter/endpoint

- Assessment van DSM Persoonlijkheidsstoornissen-IV (ADP-IV) vragenlijst ( $\alpha = .76-.77$ ; Doering et al., 2007; Schotte et al., 1998; 2004)
- Clinician-Administered PTSD Scale for DSM-5 (CAPS-5;  $\alpha = .90$ ; Boeschoten et al., 2014a; 2018)

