### 10.1 Primary study parameter(s)

The primary study parameter is the number of diagnosed PD symptoms, over five moments of measurement. In order to test the effectiveness of EMDR in reducing the number of PD symptoms over time, a linear mixed model (LMM) with intention-to-treat will be used. Within-subjects factor 'Time' has five levels (baseline vs. post-intervention vs. three-month vs. six-month vs. twelve-month follow-ups) and between-subjects factor 'Group' has two (EMDR vs. waiting list). Corrected post-hoc analyses will be performed where significant effects are found.

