### 10.2 Secondary study parameter(s)

Mixed models with intention-to-treat will be used to compare EMDR and waiting list qua (1) the decline of diagnoses of PD, (2) the severity of psychotrauma and PTSD symptoms and (3) the severity of difficulties in emotion regulation and interpersonal functioning. The economic evaluation will be undertaken according to the Dutch guidelines for costs effectiveness studies taken a societal perspective (Hakkaart et al., 2016). The severity (i.e., number of symptoms) of PD, aided by the ADP-IV, will be used for effectiveness. The TiC-P is used to collect data on utilization of medical services and productivity loss. Utility scores are estimated using the EQ-5D-5L and MHQoL will measure the effects. A cost-utility analysis and a cost-effectiveness analysis (CEA) are conducted. The cost-utility is calculated as the incremental costs and utilities, which yields a cost per QALY estimate. The cost-effectiveness is expressed in the incremental costs and scores on the SCID-5-PD.

Multilevel modeling is used to model cost-effectiveness. For assessing the uncertainty, cost effectiveness acceptability curves and cost effectiveness planes will be created after bootstrapping. The acceptability curve illustrates the probability that the cost-effectiveness ratio will be accepted for different thresholds. In a cost-effectiveness plane, both incremental costs and incremental effects are plotted to account for combinations.

Sensitivity analyses will be performed after the analysis if necessary.

Qualitative data on patients' experiences with EMDR therapy will be summarised by the researchers and provided to participants for respondent validation. The researchers will

thoroughly read all transcripts, highlight all potentially relevant excerpts and sort them based on the research questions. These sorted data will then be independently coded by the researchers; excerpts will be grouped based on their similarities. Then, these groupings will be identified/themed. Consequently, the researchers will confer and attempt to reach consensus on all groupings and themes, resulting in a preliminary codebook. The codebook and two information rich transcripts as examples will be presented to the study group. Themes will be reviewed, focussing on understanding the data and confirming that the data still correspond to the assigned themes.

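### CAPS-5 is labelled primary in the Summary and 8.1.1, while the objectives, sample size and section 10 give one primary clinical outcome (PD symptoms), so the protocol does not fix what counts as a positive trial

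*Protocol*

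**What the plan says.** **Places that make CAPS-5 primary**

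- Summary, main study parameters: "The Assessment van DSM Persoonlijkheidsstoornissen-IV and Clinician-Administered PTSD Scale for DSM-5 (primary outcomes". The same sentence lists CAPS-5 a second time, among the remaining measures.
- Section 8.1.1 has two entries. The first is the ADP-IV questionnaire and the second is "Clinician-Administered PTSD Scale for DSM-5 (CAPS-5". CAPS-5 does not appear in the secondary list in 8.1.2.

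**Places that give one primary clinical outcome, with PTSD severity secondary**

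- Summary, objective: "The aim of this study is to evaluate the effectiveness of EMDR in reducing PD symptoms".
- Section 2, primary objective 1: "How effective is EMDR therapy compared to waiting list on symptoms of PD". Primary objective 2 is cost-effectiveness; neither concerns PTSD.
- Section 2, secondary objective 4: "How effective is EMDR therapy compared to waiting list on the severity of symptoms of PTSD".
- Section 4.4: one calculation, for the ADP-IV, at alpha .05. No effect size for CAPS-5 is given.
- Section 10.1: "The primary study parameter is the number of diagnosed PD symptoms, over five moments of measurement".
- Section 10.2, second comparison among the secondary parameters: "2) the severity of psychotrauma and PTSD symptoms".

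The only correction for multiple testing is in 10.1: "Corrected post-hoc analyses will be performed where significant effects are found". It concerns follow-up comparisons after a significant effect, not two primary outcomes.

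**The concern.** These statements cannot all hold. Someone working from 8.1.1 would report two primary results. Someone working from 10.1 would report one and treat PTSD severity as supporting evidence.

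The difference matters most if the ADP-IV shows no effect and CAPS-5 does. On 8.1.1 the trial could then be presented as positive on a primary outcome. On section 2 and 10.1 it would be a null trial with a positive secondary finding. The trial's question is whether EMDR reduces PD symptoms, so the label decides what it may conclude. If either outcome sufficed at .05, the chance of a false claim would also exceed the 5% on which the sample size rests.

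**Working it through.** **1. The plan's own sample size.** Inputs from 4.4: effect size d = 0.43, correlation rho = 0.7, m = 5 measurements, alpha .05, power 0.8, two arms. Two-sided testing and 1:1 allocation are assumptions, since neither is stated. The Liu and Liang formula for a difference in group means with exchangeable correlation is

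n per arm = 2(z_alpha/2 + z_power)² × [1 + (m − 1)rho] / (m d²)

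- m = 5: 2 × (1.960 + 0.842)² × (3.8/5) / 0.1849 = 64.5, so 65 per arm and 130 in total, within 2% of the stated 132.
- m = 4: 2 × (1.960 + 0.842)² × (3.1/4) / 0.1849 = 65.8, so 66 per arm and exactly 132.
- One-sided .05 with m = 5 gives 102, which does not match.

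The 132 is therefore a calculation for one outcome tested once at two-sided .05. It makes no allowance for a second primary outcome.

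**2. Error rate under each reading of the protocol.**

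*One primary outcome (10.1 read alone).* One test at .05, so the error is 5%.

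*Two primary outcomes, both needed.* A false claim requires both tests to be significant while at least one null hypothesis is true. Its probability cannot exceed that of a single false rejection, so it is at most 5%.

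*Two primary outcomes, either sufficient.* For independent tests: 1 − (1 − .05)² = 0.0975. For correlated tests: 1 − P(|Z1| < 1.96 and |Z2| < 1.96) under a bivariate normal distribution. The protocol gives no correlation between the two tests, so a range is shown.

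| Assumed correlation | Family-wise error |
|---|---|
| 0 | 9.75% |
| .3 | 9.5% |
| .5 | 9.1% |
| .7 | 8.3% |
| .9 | 7.0% |

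**3. Fixed sequence, ADP-IV then CAPS-5, each at .05.** If the ADP-IV null is true, any false claim requires a false rejection on ADP-IV, which has probability at most .05. If the ADP-IV null is false, the only possible false claim is on CAPS-5, again at most .05. The family-wise error stays at .05 and the ADP-IV test keeps its full alpha, so the 132 is unaffected.

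**4. Cost of requiring both.** If each outcome had 80% power (an assumption for CAPS-5), the power for both would be 0.8 × 0.8 = 64% if independent, and about 67% to 71% at correlations of .3 to .7. The protocol makes no provision for that loss.

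**The case against.** **The analysis section is clear, so this may be a drafting slip.** Section 10.1 speaks of one primary parameter, and the Summary objective, Objective 1 and 4.4 agree. The double listing of CAPS-5 in the Summary also looks like an editing error. That stands as an account of what was probably meant. It does not remove the conflict, because 8.1.1 is the section that defines the endpoints, and it lists two.

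**CAPS-5 is not named in section 2 or 10.2.** Both speak of PTSD symptom severity, which the PCL in 8.1.2 also measures. One could thus read CAPS-5 as primary and the PCL as the secondary measure. The premise is correct, but the reading does not work: the same construct would be both primary and secondary, no primary objective would correspond to CAPS-5, and 10.1 and 4.4 would still ignore it.

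**Multiplicity rules may sit in a statistical analysis plan.** Agreed, and the absence of such a rule is not the point here. The conflicting label is in the protocol itself, and a later plan could follow one section only by departing from another.

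**Stronger readings that the protocol does not support**

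- A reader might infer that the trial's error rate is above 5%. No section says that success on either outcome is enough, so the figures of 7.0% to 9.75% are conditional on a rule that is left open, not stated.
- A reader might infer that CAPS-5 is the outcome more likely to be positive, because EMDR is described as established for PTSD. Section 4.2 requires distress from traumatic experiences, not PTSD. Section 1 cites PTSD prevalences of 34% to 56% in borderline PD and 20% to 47% in other PD, and no CAPS-5 effect size is given.
- A reader might infer from the word diagnosed in 10.1 that the primary measure is the SCID-5-PD interview. Sections 4.4 and 10.2 tie the symptom count to the ADP-IV, so this is a loose word and not a second contradiction.

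**Conclusion.** The point holds as an internal contradiction about the status of CAPS-5, and it is wrong as written. The consequence is that the protocol does not fix whether a positive CAPS-5 with a null ADP-IV is a positive trial.

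The numerical size is conditional. The error reaches 7.0% to 9.75% if either outcome may carry the trial, assuming two-sided tests at .05 and a correlation between .9 and 0. Under either of the other two readings it is at or below 5%. The sample size reproduces, within rounding and the choice of m, for a single ADP-IV test, which supports treating PD symptoms as the sole primary clinical outcome.

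**What to change.** - **Summary and 8.1.1:** make the number of PD symptoms on the ADP-IV the sole primary clinical endpoint.
- **8.1.2:** add CAPS-5 as a secondary endpoint. In the Summary, keep it once, among the secondary measures.
- **10.1:** name the ADP-IV as the source of the symptom count and drop the word diagnosed.

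If the investigators want CAPS-5 to remain primary, state a fixed sequence: CAPS-5 is tested at .05 only after ADP-IV is significant at .05. Alpha stays at .05 and the stated sample size is unchanged. Power for CAPS-5 would still be undocumented, because 4.4 gives no effect size for it.

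The cost is a wording amendment to the Summary, 8.1.1, 8.1.2 and 10.1, with no change to data collection or numbers. It should be made before outcome data are seen; afterwards the choice of primary outcome could be questioned. Cost-effectiveness, the second primary objective, is not affected by this change.

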## 1. INTRODUCTION AND RATIONALE

### Statement of the problem

Prevalence rates for childhood trauma among patients with personality disorders (PD) are very high. Verbal -, physical - and sexual abuse during childhood have been reported in, respectively, 72%, 46% and 26% of patients with borderline personality disorder (BPD, Zanarini, Gunderson, Marino, Schwartz, & Frankenburg, 1989). A total of ninety-seven percent of BPD patients were found to have experienced at least one type of childhood trauma, i.e., emotional -, physical – or sexual abuse, or emotional – and physical neglect at our department. Among different types of PD high prevalence rates were reported for abuse (73%) and neglect (82%, Battle et al., 2004). Estimates of the prevalence of PTSD in patients with BPD range 34% to 56% (Slotema, Blom, Niemantsverdriet, Deen & Sommer, 2018; Zanarini et al., 1998). For patients with other PD than BPD prevalence rates for PTSD vary between 20 and 47% (Goldstein et al., 2017; Zanarini et al., 1998; Yen et al., 2002). Psychotherapy is the treatment of first choice for patients with PD. However, training of therapists and the long duration of treatment are accompanied with high costs. Furthermore, symptoms are found to remain unchanged or exacerbate during psychotherapy for PD in 34 up to 57% (Giesen-Bloo et al., 2006; Svartberg, Stiles, & Seltzer, 2004; own data from clinical practice). Given these concerns, the high prevalence of trauma and associated consequences, the question arises whether treatment of patients with PD can be improved if interventions will be used that focus on trauma memories. There is mounting evidence suggesting that EMDR therapy is not only effective in the treatment of PD with and without PTSD but also efficient, and thus cost-effective. The need to improve the treatment of PD with interventions that focus on trauma is clear. The next step is to conduct a sufficiently powered RCT for patients with all types of PD to explore the efficacy and cost-effectiveness of EMDR compared to waiting list to confirm these preliminary results and to determine the effects in terms of loss of diagnoses and cost-saving one year following treatment.

### Background

Personality disorders (PD) occur in 4-13% of the North American and European population (Tyrer, Reed, & Crawford, 2015), and 40-50% of patients in mental health care settings meet the diagnostic criteria for PD (Newton-Howes et al., 2010). Patients with PD suffer from low self-esteem and have severe impairments in the regulation of emotions and interpersonal functioning. Their quality of life is low and societal costs are high. Most studies in this area included patients with borderline personality disorder (BPD), in which PTSD is present in 34 up to 56% (Slotema et al., 2018; Zanarini et al., 1998). Patients with BPD and PTSD have a lower quality of life, more comorbid disorders and a higher risk for suicide attempts than patients with only one of those diagnoses. Although up to 66% of patients with BPD do not

fulfill the criteria for PTSD, 97% of them were found to have experienced at least one type of childhood trauma, including abuse and neglect (own data). Patients who have suffered from childhood trauma are in risk to have dysregulation of their emotions, hallucinations, suspiciousness, difficulties in attachment and to be revictimized during their lives (Niemantsverdriet et al., 2017; Zanarini, 2000; Voestermans et al., 2020; Seo & Choi, 2018). Although less extensively investigated, Battle and colleagues (2004) found that rates of childhood maltreatment among individuals with different types of PD are high, with 73% of their sample reporting abuse and 82% reporting neglect. Prevalence rates for PTSD among other PD than BPD range 20 to 47% (Goldstein et al., 2017; Zanarini et al., 1998; Yen et al., 2002).

Multidisciplinary treatment guidelines state that cognitive behavioral therapy (CBT) and eye movement desensitization and reprocessing (EMDR) therapy are the treatments of choice for PTSD (de Jongh, Amann, Hofmann, Farrell, & Lee, 2019). A meta-analysis of four RCTs with psychotherapy (other than EMDR therapy) for PTSD in BPD revealed effect sizes ranging .54-.82 and the interventions were safe (Slotema, Arends, & Franken, submitted). Results for the influence of psychotherapy for PTSD on symptoms of PD are inconclusive (see for example Markowitz et al., 2015 and Kredlow et al., 2017). The same holds true for EMDR therapy in that the effects of EMDR on interpersonal functioning has barely been explored with one RCT revealing negative results for social functioning among patients with chronic psychotic disorders and comorbid PTSD (de Bont et al., 2016).

Although the literature suggests that EMDR therapy is more efficient, cost-effective and better tolerated than other interventions (including CBT; McQuire, Lee, & Dummond, 2014; de Jongh et al., 2019; Mavranetzouli et al., 2020), EMDR has not been studied thoroughly in populations with PD. In an open study EMDR appeared to be beneficial and safe in patients with PD for PTSD (Slotema, van den Berg, Driessen, Wilhelmus, & Franken, 2019). No differences in severity of PTSD or efficacy of EMDR could be found between patients with BPD and other PD. De Jongh and colleagues (2020) established a significant reduction in PTSD symptoms with a combination of EMDR, prolonged exposure therapy, physical activity, and psychoeducation without any form of stabilization within only 8 treatment days. Of interest is that BPD symptoms decreased and one third of the patients lost their positive screen for BPD posttreatment. Furthermore, results of an RCT comparing five sessions of EMDR therapy to waiting list in patients diagnosed with PD without PTSD revealed medium to large effect sizes for psychological symptoms, psychological functioning, and personality functioning without any adverse events (Hafkemeijer, de Jongh, van der Palen, & Starrenburg, submitted). These findings are particularly important because the length of treatment was brief in that patients received only a total of 7.5 hours of EMDR therapy, whereas the gains were maintained at the end of the study, i.e., at 3-month follow-up. This is

remarkably shorter than in previous studies on the treatment of BPD, including Harned, Korslund, & Linehan (2014) whose patients received one full year of dialectical behavior therapy (DBT), existing of weekly sessions of individual therapy and group skills training later combined with the DBT prolonged exposure protocol, and has a much lower intensity of treatment than a 12-week residential of DBT, music – and art therapy, PTSD-specific psychoeducation and trauma-focused CBT (Bohus et al., 2013).

